## Abstract

**Background:**

Significant mental health disparities exist for Hispanic populations, especially with regard to depression treatment. Stigma and poor communication between patients and their providers result in low use of antidepressant medications and early treatment withdrawal. Cultural factors which influence treatment decisions among Hispanics include fears about the addictive and harmful properties of antidepressants, worries about taking too many pills, and the stigma attached to taking medications. Primary care settings often are the gateway to identifying undiagnosed or untreated mental health disorders, particularly for people with co-morbid physical health conditions. Hispanics, in particular, are more likely to receive mental healthcare in primary care settings. Recent recommendations from the U.S. Preventive Services Task Force are that primary care providers screen adult patients for depression only if systems are in place to ensure adequate treatment and follow-up.

**Methods:**

We are conducting a randomized controlled trial among 150 depressed adult Hispanics in a primary care safety net setting, testing the effectiveness of a culturally appropriate depression education intervention to reduce stigma and increase uptake in depression treatment among Hispanics, and implement a Measurement-Based Integrated Care (MBIC) model with collaborative, multidisciplinary treatment and culturally tailored care management strategies.

**Discussion:**

This study protocol represents the first randomized control trial of the culturally adapted depression education *fotonovela*, *Secret Feelings*, among Hispanics in a primary care setting. The education intervention will be implemented after diagnosis using an innovative screening technology and enrolled in measurement-based integrated care for the treatment of depression, which will help build the evidence around cultural adaptations in treatment to reduce mental health disparities.

**Trial registration:**

ClinicalTrials.gov, NCT02702596. Registered on 20 March 2016.

**Electronic supplementary material:**

The online version of this article (doi:10.1186/s13063-017-2109-y) contains supplementary material, which is available to authorized users.

## Background

### Chronic disease and depression

Chronic medical conditions affect nearly half of the people in the United States and two-thirds of encounters with health professionals are for the management of those conditions [1]. Effective treatment of chronic illness is complicated and requires significant investment on the part of the patients and their families. More than 300 million people worldwide were living with depression in 2015, making it the leading cause of medical disability in the world, causing significant disease burden and medical cost [2]. One in six Americans is afflicted in their lifetime and chronicity is common [3].

Adults with chronic medical conditions have high rates of depression and anxiety which often impair self-care and compliance with treatment of their disease [4]. For patients with diabetes, depression severity is associated with diabetes complications, medical co-morbidity, greater anxiety, dysthymia, financial worries, social stress, and poorer quality of life [5]. Major depression increases the burden of chronic illness by increasing perception of symptoms, causing additional impairment in functioning, and increasing medical cost through over-utilization of the healthcare system [4]. Many patients with co-morbid depression and chronic disease may sabotage their own treatment by “focusing on the physical” and delaying treatment of mental health concerns for weeks or months. Such delays in addressing the underlying depression cannot only make remission difficult, but can make treatment of the physical condition challenging [6].

### Risk factors for Hispanics and depression

A national sample of Hispanics has estimated the prevalence of depression among the population to be 27% [7]. Hispanics have double the risk of co-morbid depression and diabetes, with rates as high as 33%, compared with the general population [8]. Response to depression treatment in Hispanics is slow and relapse rates are high, which may explain the early discontinuation of medication without consulting their provider [9, 10]. Hispanic patients often voice fears about the addictive and harmful properties of antidepressants, worries about taking too many pills, and the stigma attached to taking medications [11, 12]. In the context of co-morbid chronic disease, depression can be difficult to detect by primary care providers, especially where screening for depression is inconsistent, creating further barriers to treatment [13].

Lack of English fluency is associated with reduced healthcare use [14]. Limited English proficiency (LEP), limited health literacy, geographic inaccessibility, and lack of medical insurance are all more common among immigrants, minority populations, individuals of low socioeconomic status, and people in rural areas. The citizenship, or legal status of an individual, impacts the extent to which they can secure quality healthcare, as does the level of acculturation and duration of residence in the U.S. [15]. Individuals with LEP are less likely to self-identify a need for mental health services, which subsequently predicts lifetime mental healthcare use, and results in longer duration of untreated disorders [16, 17].

### Integrated care

Integrated care is a systematic approach to the treatment of depression in primary care that involves systematic screening for depression, the integration of a care manager, with primary care provider oversight and psychiatric consultation, as needed, to more proactively treat mental health problems [4]. The primary function of the care manager is to manage the mental health disorders of the patients, monitor their response to treatment, and facilitate communication between the patient, the primary care providers, and the consulting psychiatrist [18, 19]. The functions of the care manager can address significant barriers to treatment such as stigma, limited knowledge of mental health disorders, poor doctor–patient communication, and treatment engagement and adherence, which disproportionately affect racial and ethnic minorities [19, 20]. However, those functions may be limited unless culture specific strategies are employed to engage and retain minority patients and those with LEP in treatment [21, 22].

### Patient education

While patient education has been established as essential in chronic disease management [23], less is known about its role in engagement and improved outcomes for mental disorders [24]. Low health literacy is related to poor management of chronic diseases, lack of basic knowledge about medical conditions and treatments, less understanding and use of preventive services, worse health outcomes, and higher rates of hospitalization and emergency care use [25]. However, qualitative evaluation of conceptual models which include comprehensive educational interventions for depressed Hispanics have found patients were optimistic about the benefits of treatment [26], especially those which adapt materials for literacy and cultural content, and include homework materials that are linguistically and idiomatically appropriate [5].

### Aims and objectives

The study aims to examine a novel culturally adapted patient education intervention to increase engagement by Hispanics in depression treatment. The intervention will be implemented after diagnosis using an innovative screening technology and via measurement-based integrated care for the treatment of depression, which will have a substantive impact on reducing mental health disparities in the Hispanic population.

#### Specific aim 1

Examine the specific effects of a Depression Education *Fotonovela* (DEF) to increase knowledge of depression, reduce stigma, and increase engagement in depression treatment among Hispanic patients.

#### Specific aim 2

Evaluate the impact of measurement-based integrated care (MBIC) on retention in treatment and remission of depression symptoms in one community-based Federally Qualified Health Center (FQHC) in North Texas whose patient population is majority Hispanic.

#### Specific aim 3

Examine the feasibility of universal screening and accurate detection of depression among adult primary care patients utilizing innovative iPad Depression Screening technology.

## Methods/Design

### Setting and participants

The study will take place at one FQHC whose mission is to provide a community medical home through accessible, compassionate, and quality healthcare services. The center offers a full range of comprehensive primary and preventive services, including childhood immunizations and physical exams, adult physical exams, management of chronic illnesses, family planning services, maternity care services, and health education promotion. In 2015, the center served 11,895 unduplicated patients for a total of 25,362 patient visits. Of those patients, 90% were Hispanic and the majority did not speak English. There are currently five physicians and four mid-level providers (physician assistants and nurse practitioners) working at the center.

The target enrollment is 150 patients over the 24-month enrollment period. All adult primary care patients at the center will be asked to participate in screening for depression with the iPad Depression Screening application (universal screening). After being informed about the expectations for participation in the study and the compensation payments, it is expected that a minimum of 2–3 patients per week will agree and be enrolled in the study. Patients who meet study inclusion criteria will be enrolled on a first-come, first-serve basis until the target of 150 patients is reached. The study protocol was reviewed and approved by the Institutional Review Board of the University of Texas at Arlington. All patients will provide written informed consent to participate.

### Intervention

The study will compare outcomes among patients randomly assigned to one of two treatment conditions: (1) MBIC with DEF (MBIC + DEF); or (2) MBIC with standard education (MBIC + SE). All patients enrolled in the Measurement, Education and Tracking in Integrated Care (METRIC) study will receive MBIC. The schedule of enrollment, interventions, and assessments is outlined in Fig. 1, study flow is outlined in Fig. 2, and page listings for all study components can be found in the Standard Protocol Items: Recommendations for Interventional Trials (SPIRIT) Checklist (see Additional file 1).

**Fig. 1 Fig1:**
[figure not shown]
Schedule of enrollment, interventions and assessments

**Fig. 2 Fig2:**
[figure not shown]
Study flow diagram

#### Depression Education Fotonovela

This study will test a unique, culturally adapted DEF titled *Secret Feelings*, developed by Cabassa, Molina, and Baron [27]. Developed as a comic-book style pamphlet using photographs and dialogue bubbles, the *fotonovela* is written at a 4th-grade reading level and presents information on depression symptoms and treatment while portraying a soap opera-style dramatic story. This *fotonovela* is an Entertainment-Education (EE) approach which has demonstrated early success as an effective tool for engaging Hispanic audiences and increasing knowledge about specific health issues [28–30]. The DEF differs from typical patient education materials by incorporating surface and deep-level cultural elements including the use of simple language, attractive visuals, cultural norms, and educational messages that target specific misconceptions and attitudes about depression and depression treatment common among Hispanics [30, 31]. See Figs. 3 and 4 for sample images of the *fotonovela* covers.

**Fig. 3 Fig3:**
[figure not shown]
Depression *fotonovela* cover–English

**Fig. 4 Fig4:**
[figure not shown]
Depression *fotonovela* cover–Spanish

The DEF is designed to enhance the awareness and understanding of depression, its role in chronic disease, its impact on Hispanic populations, and the multitude of barriers to effective treatment in a culturally meaningful way. The *fotonovela* has demonstrated significant improvements in depression knowledge and reductions in stigma toward antidepressants and mental health treatment in a community education setting and a multiservice community clinic setting but has not been tested as a depression treatment engagement in a primary care setting [32, 33].

#### Measurement-based integrated care

This project will implement MBIC, which synthesizes the science of integrated healthcare and incorporates the strategies of measurement-based care, often missing from existing models [34]. The MBIC intervention is based on the principles of collaborative care developed by Unutzer and Katon [35] at the University of Washington and adapted to include measurement-based treatment strategies developed by Trivedi and colleagues [36]. Abundant evidence supports the conclusion that a measurement-based approach significantly improves outcomes and lowers costs, especially when coupled with care managers. Although Trivedi et al. [36] have led successful development of measurement-based strategies, measurement-based care is still seldom used in treating patients with depressive disorders. The concept of MBIC for the treatment of depression includes: the systematic assessment of symptoms; antidepressant treatment side effects and medication adherence; and the incorporation of a depression care manager (DCM) to track patients and keep them engaged in care using behavioral interventions.

In this study, a DCM will engage the patient in treatment, assess barriers to treatment, and develop solutions to barriers. The DCM will be a bilingual, licensed Masters level clinical social worker (LCSW) and have specialized training in brief psychotherapy and interventions demonstrated effective in primary care settings, such as Problem Solving Treatment for Primary Care (PST-PC) [37] and Behavioral Activation (BA) [38]. The DCM will also work closely with the patients’ primary care provider (PCP) in the development and execution of treatment plans which will include counseling and/or pharmacotherapy. Using measurement-based care treatment principles, patients’ depressive symptoms will be measured at defined intervals, along with antidepressant treatment side effects and treatment adherence (if applicable). Measuring mental health symptoms at the start of a patient’s treatment and regularly thereafter facilitates treatment planning and adjustment, indicates when it is time to start or change medications, avoids patients staying on ineffective treatments for too long, and assists PCPs in knowing when to refer for consultation or get additional help.

### Study procedures

#### Universal screening with iPad technology

The project will utilize a novel technology to systematically identify depressed patients, quantify the severity of their depression, and guide treatment recommendations. The web-based software platform is designed to support the use of MBIC by providing feedback to providers at the point of care. All adult primary care patients will be asked to complete the iPad Depression Screening (universal screening) at the annual visit and at new/non-acute visits. During the routine intake process, designated clinical staff will give the patient the iPad and ask them to complete the screening for depression. The iPad Depression Screening will be presented in English or Spanish, depending on the patient’s preference. The first screen in the iPad application is presented to record consent and the patient will be informed that refusal to consent for screening will have no effect on the care they receive at the clinic. If the patient does not consent, the screening process will be terminated and the patient will continue with their scheduled visit.

The iPad Depression Screening application begins with the nine-item Patient Health Questionnaire (PHQ-9) [39]. If the patient screens positive for depression, indicated by a score of ≥ 5, the screening application immediately offers the Generalized Anxiety Disorder (GAD-7) [40] anxiety measure. Once completed, an electronic notification is generated to the DCM and patient’s PCP and the application screen will lock with a message to return the iPad to a clinic staff member.

Immediately after a patient screens positive for depression, the medical assistant will document the PHQ-9 score in the patient’s electronic health record (EHR) and will inform the provider that the patient screened positive for depression to enable the provider to interpret the depression score. Patients who screen positive for depression but previously had a diagnosis of depression and are in treatment will be excluded from enrollment in the study. Because of the specificity of the stigma measurements and the *fotonovela* being tested, self-identified non-Hispanic patients will also be excluded from enrollment in the study. Figure 2 summarizes the screening, study eligibility, randomization, group allocation, and study flow.

#### Randomization

After a patient screens positive for depression with the iPad Depression Screening application, the provider will immediately facilitate an introduction to the DCM for potential enrollment in the study. The DCM will assess for the presence of the nine diagnostic criteria for major depression from the Diagnostic and Statistical Manual of Mental Disorders (DSM-IV) [41] through a clinical interview. Once the depression diagnosis is confirmed, patients will be offered the opportunity to participate in the study, guided through the informed consent process and randomized to one of two treatment groups. A block randomization list that randomizes 150 participants into 75 blocks will be generated through an online randomization website and will be kept in a locked filing cabinet in the DCM’s office. Patients will be assigned to the group that coordinates with their patient enrollment number on the randomization list. One hundred and fifty patients will be randomly assigned to two possible treatment arms: (1) MBIC + DEF; or (2) MBIC + SE. A randomization log will be maintained by the Project Coordinator, which will include treatment assignment, names of participants, and participant identification numbers.

At the baseline visit, the DCM will have the patient complete all study measures and engage the patient during the regular intake process. The DCM will document the patient’s PHQ-9 screening score, the stigma measures, current treatment preferences (pharmacotherapy, counseling), and potential barriers to care in a research database. The DCM will also explain the compensation schedule, which includes payment for completing measures after the education intervention and each follow-up research visit, and schedule the patient’s education visit and first MBIC appointment to take place after the education visit.

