### Measures/Assessments

Demographic information will be collected from each participant to include gender, age, marital status, level of education, and co-morbid medical conditions (self-report). Three brief mental health measures will be collected via the iPad Depression Screening and Monitoring application technology by clinical staff and transferred to the research database by research staff. All research and clinical trial data will be collected via REDCap (Research Electronic Data Capture), a secure, web-based application used for a variety of research and maintained by Vanderbilt University Office of Research [43]. All measures have been validated in Spanish.

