#### Patient Health Questionnaire-9 (PHQ-9)

The PHQ-9 is a self-report measure that assesses the frequency of symptoms on each of the nine DSM-IV [41] criteria for depression for “the last two weeks.” Responses for each item are scored as 0 for “not at all,” 1 for “several days,” 2 for “more than half the days,” and 3 for “nearly every day,” which results in a range of possible scores of 0–27. Total scores of 5–9 represent mild depression, 10–14 represent moderate depression, 15–19 represent moderately severe depression, and > 20 represent severe depression. Patients with a PHQ-9 score ≥ 10 are considered to have clinically significant depressive symptoms. The PHQ-9 has been shown to be a reliable and valid measure of depression severity in primary care samples with a Cronbach’s alpha of 0.89 and has demonstrated construct validity among African American, Hispanic, and non-Hispanic white populations [44, 45]. The PHQ-9 is designed to provide necessary information about potential depression diagnoses while not overburdening patients and providers. The PHQ-9 will be administered via the iPad screening and monitoring application at screening and all follow-up MBIC and research visits.

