#### Generalized Anxiety Disorder-7 (GAD-7)

The GAD-7 is a seven-item self-report scale for identifying the presence of generalized anxiety disorder (GAD) and assessing symptom severity. The items of the GAD-7 are based on the diagnostic criteria for GAD in the DSM-IV and assess frequency of symptoms over the last two weeks using four response options: “not at all,” “several days,” “more than half the days,” and “nearly every day,” scored as 0, 1, 2, and 3, respectively. A score of 10 or greater on the GAD-7 represents a point for identifying cases of GAD. Cut points of 5, 10, and 15 represent mild, moderate, and severe levels of anxiety, respectively. The reliability of the GAD-7 in primary care settings, as well as in the general population, has demonstrated excellent internal consistency reliability with a Cronbach’s alpha of 0.92 and 0.89, respectively [40]. The GAD-7 will be administered after a positive screen for depression and at all follow-up visits. The GAD-7 will be administered via the iPad screening and monitoring application at screening at all follow-up MBIC and research visits.

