The evaluation of Aim 1 will examine the specific effects of the MBIC + DEF to increase knowledge about depression, reduce stigma, and increase engagement in depression treatment compared to MBIC + SE as measured by the following:Changes in knowledge of depression among Hispanic patients pre and post DEF compared with SE, as measured by the DKM. The DEF group is expected to report significantly greater DKM scores over time when compared with the SE group indicating gains in depression knowledge following receipt of depression education.Changes in attitudes among Hispanic patients toward depression pre and post DEF compared with SE using the SCMHC, LSAS, and the SD measures. The DEF group is expected to report significant changes in SCMHC, LSAS, and the SD over time when compared to the SE group and reported reductions in stigma related to mental health and psychiatric medications following depression education.Determine engagement in depression treatment for patients in DEF vs. SE.Quantify the number of patients diagnosed with depression and received the DEF intervention who went on to begin depression treatment compared with SE. The DEF group is hypothesized to have a greater portion of individuals engaging in depression treatment than the SE group following treatment. Furthermore, participants in the DEF group will have an increased likelihood of later engaging in treatment following the intervention.Quantify which treatment modality the patient with depression chose after the DEF compared to SE: pharmacotherapy; counseling; or other behavioral intervention. The DEF group is hypothesized to have a greater portion of individuals engaging in pharmacotherapy, counseling, or other behavioral interventions than the SE group following treatment. Furthermore, participants in the DEF group will have an increased likelihood of later engaging in pharmacotherapy, counseling, or other behavioral interventions following the depression.

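### The text places the baseline knowledge and stigma measures after randomization, at a visit run by the care manager whose office holds the allocation list

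*Protocol article*

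**What the plan says.** The first paragraph of the Randomization section sets out the steps: the DCM confirms the diagnosis by interview, and patients are then offered the study, "guided through the informed consent process and randomized to one of two treatment groups". The arm follows from the enrollment number on a list kept in a locked cabinet in the DCM's office. The Project Coordinator maintains the randomization log.

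The second paragraph turns to the baseline visit: "At the baseline visit, the DCM will have the patient complete all study measures and engage the patient during the regular intake process". It continues: "The DCM will document the patient’s PHQ-9 screening score, the stigma measures, current treatment preferences (pharmacotherapy, counseling), and potential barriers to care". At the same visit the DCM schedules the education visit, which takes place within a week (Education section).

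The section on the Depression Knowledge Measure lists baseline, post-education, one-month, six-month and 12-month administrations for the DKM and the three stigma scales. For the PHQ-9 the stated times are different: "The PHQ-9 will be administered via the iPad screening and monitoring application at screening and all follow-up MBIC and research visits".

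Aim 1 in the Analysis section rests on pre/post comparisons, for example "Changes in knowledge of depression among Hispanic patients pre and post DEF compared with SE, as measured by the DKM", with a parallel item for the stigma scales. The analysis uses available data from participants who have baseline data.

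**The concern.** A baseline does two jobs in a randomized comparison of change: it is the reference point for each patient, and it should be unrelated to the arm except by chance. The second property is guaranteed only if the value is obtained before the arm is known. If the DKM and stigma scales are completed after assignment, under a DCM who can know the arm, the way questions are explained or prompted could differ between arms.

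The stigma scales leave room for this. Items answered with the don't-know/refuse option are left out of the sum, so each one contributes nothing to the total, exactly as a zero would. On the SCMHC (three items, range 0–3), one item is a third of the range.

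Two things are at stake. First, a baseline shift by arm enters the between-arm difference in change in full. Second, a patient who is assigned but leaves before finishing the questionnaires has no baseline and drops out of the analysis after randomization, which sits badly with the stated intent-to-treat approach.

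**Working it through.** **1. Order of events, measure by measure (protocol article).**

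| Measure | First administration stated | Before assignment? |
|---|---|---|
| PHQ-9 | iPad screening: "The iPad Depression Screening application begins with the nine-item Patient Health Questionnaire (PHQ-9") | Yes |
| GAD-7 | iPad screening: "The GAD-7 will be administered after a positive screen for depression and at all follow-up visits" | Yes |
| PAQ | Follow-up visits, patients on medication | No baseline |
| DKM | Baseline visit with the DCM | Not secured; described after randomization |
| SCMHC, LSAS, SD | Baseline visit with the DCM | Not secured; described after randomization |
| Treatment engagement | Dichotomous, after education | Not a change score |

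The issue is confined to the DKM and the three stigma scales.

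**2. Can the DCM know the arm at that visit?** The list is in the DCM's office. The DCM books the education session. The Education section gives each of the two research assistants one arm only, and the sessions differ in length (about 20 min for SE, 30–45 min for DEF). Booking the right person and slot would ordinarily require the arm. Nothing in the article blinds the DCM.

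**3. What a shift would do (illustration).** The plan gives no figure on this point, so there is none to reproduce. Inputs:
- n = 56 evaluable per arm, borrowed from the Sample size section, where it was set for depression scores;
- two-sided 5% test;
- baseline/follow-up correlation r = 0.5 or 0.7 (assumed);
- arm-related baseline shift d = 0.1, 0.2 or 0.3 SD (assumed);
- equal SD at both times, no true effect, and the shift present at baseline only.

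The variance of one patient's change is 2(1 − r) in SD² units. The standard error of the between-arm difference in change is therefore SE = √(2 × 2(1 − r)/n).
- r = 0.5: √(4 × 0.5/56) = 0.189
- r = 0.7: √(4 × 0.3/56) = 0.146

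Rejection probability = P(Z > 1.96 − d/SE) + P(Z < −1.96 − d/SE).

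| d (SD) | r = 0.5 | r = 0.7 |
|---|---|---|
| 0.1 | 0.083 | 0.105 |
| 0.2 | 0.185 | 0.277 |
| 0.3 | 0.355 | 0.536 |

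With all 75 per arm, SE at r = 0.5 falls to √(2/75) = 0.163 and the three probabilities become 0.094, 0.232 and 0.451. A bias does not shrink with sample size, so a larger n makes a false rejection more likely.

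This is a two-time-point contrast. The planned mixed-design ANOVA has up to five time points for these scales, so its rejection rates would differ. Baseline remains one of the levels being contrasted.

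**The case against.** **The order is an inference.** The baseline paragraph opens without any word such as 'then', may simply describe what the visit contains, and could refer to the same visit as consent. The schedule and flow are in Figs. 1 and 2, which are not shown and may settle the matter. This stands, and it limits confidence. It does not remove the point, because the only sequence in the text puts randomization first.

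**Nobody is named as the person who assigns.** A reader might infer that the DCM has just assigned the arm. The article says only that the arm follows the enrollment number and that the Project Coordinator keeps the log. What is supported is access to the list and the task of booking the education visit.

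**A reader might extend the point to every change score, including the PHQ-9.** The documents do not support that. The PHQ-9, whose change is the primary outcome for Aim 2, is completed at screening before the diagnostic interview, consent and randomization, and the screening score is what the DCM documents. The Measures section adds: "Three brief mental health measures will be collected via the iPad Depression Screening and Monitoring application technology by clinical staff". The instruction to complete all study measures at baseline could suggest a repeat PHQ-9, but the PHQ-9 section lists only screening and follow-up visits. Nor is all of Aim 1 affected: engagement and choice of modality are not changes from baseline.

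**The baselines precede the education session.** Correct. They are valid pre-intervention values, and the education cannot have contaminated them. The remaining route is influence of known allocation.

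**The size is assumed.** Nothing in the article supports a particular shift or its direction, and nothing suggests that early loss would differ by arm. This stands; the table is illustrative only.

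**Reordering leaves the DCM near the list.** With 150 patients in 75 blocks (150/75 = 2 per block), a DCM who can see the list or recall the last assignment could anticipate the next one. That is a matter of concealment, separate from assessment order, and the fix here does not resolve it.

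**Conclusion.** The point holds for the baseline DKM, SCMHC, LSAS and SD. Followed as written, the Randomization section does not secure these four as pre-randomization values taken without knowledge of the arm. Four Aim 1 outcomes are exposed, and patients lost between assignment and questionnaires would leave the analysis after randomization.

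The size of the bias cannot be derived from the document. Under the assumed shifts of 0.1 to 0.3 SD with 56 per arm, a true null would be rejected about 8% to 35% of the time at r = 0.5 and about 10% to 54% at r = 0.7. These figures show sensitivity; they are not estimates for this trial.

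The conclusion rests on reading the order from the text without Figs. 1 and 2, and on the DCM being able to know the arm at the baseline visit. Severity is moderate and confidence medium.

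**What to change.** Revise the Randomization section so that, after diagnosis and consent, the patient completes the DKM, SCMHC, LSAS and SD, and treatment preferences and barriers are recorded. These are saved with a time stamp in REDCap, which the trial already uses. Only then is the enrollment number issued and the assignment read. State that a patient is randomized only once these measures are complete, and make the schedule and flow figures agree.

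If the clinic already works in this order, one clarifying sentence is enough.

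The cost is a reordering of steps within existing contact, with no added visit, staff or measure. The one downside is small: patients who stop during the questionnaires are not randomized.
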